**Follow Up (Week 26; Year 1 to year 10)**

Approximately 26 weeks and from year 1 to year 10 after completing the intervention, participants will be asked to return for a follow up visit. Body weight, waist circumference, fat mass, heart rate and blood pressure will be measured using standardized procedures and information regarding participant demographics and menopausal status (of female participants only) will be collected. Participants will complete questionnaires assessing quality of life (Short Form 36; University of Toronto Atrial Fibrillation Severity Scale), symptom burden (Canadian Cardiovascular Society Severity of Atrial Fibrillation Scale), functional capacity (Duke Activity Status Index), anxiety and depression (Hospital Anxiety and Depression Scale), insomnia (Insomnia Severity Index) and sleep apnea (STOP-BANG Sleep Apnea Questionnaire). Participants will also complete a 6-minute walk test.

Participants will be provided with an Actigraph motion sensor, to be worn for 7 days, and complete a daily FITT log over the 7-day period. They will also complete the 7-day symptom diary to record atrial fibrillation symptoms and a 7-day sleep diary to record sleep patterns. Depending on when participants are enrolled in the study, they may or may not be within the time frame to complete all of these visits.

**Primary Outcome & Primary Measures (endpoints):**

There will be two primary outcomes: 1) changes in quality of life measured by the Short Form 36 Health Survey Questionnaire (SF-36); and, 2) changes in exercise capacity measured by the 6 minute walk test (6MWT) over the 12 week intervention period.

Quality of life: will be measured using the widely used and thoroughly validated SF-36 questionnaire. It yields an 8-scale profile of functional health and well-being scores as well as psychometrically-based physical and mental health summary measures.

Exercise capacity: will be measured using the 6MWT. Patients will be instructed to walk as far as possible for 6 minutes. The 6MWT is highly reproducible, and 6MWT distance performance is highly correlated with objective measures including VO2peak and survival.

**Secondary Measures**

Secondary measures will include: 1) exercise adherence measured by accelerometer (and verified using a 7-day FIIT log; 2) activity status measured by the Duke Activity Status Index (DASI); 3) atrial fibrillation specific quality of life measured by the University of Toronto Atrial Fibrillation Severity Scale (AFSS); 4) symptom burden measured by the Canadian Cardiovascular Society Severity of Atrial Fibrillation (CCS-SAF) scale; 5) self-reported symptom frequency and severity measured by the 7-day symptom diary; 6) anxiety and depressive symptoms measured by the Hospital Anxiety and Depression Scale (HADS); 7) insomnia severity measured by the Insomnia Severity Index; 8) sleep apnea risk measured by the STOP-BANG Sleep Apnea Questionnaire; and 9) self reported sleep patterns measured by the 7-day sleep diary.

1. Exercise adherence: will be measured directly and by self-report. The Actigraph GT3X accelerometer will be used for direct measurement and worn over the right hip for a 7-day recording period. The activity monitor provides physical activity measurements including activity counts, intensity levels and energy expenditure. A FITT (frequency, intensity, time, type) log will be used to gather weekly self-reported data of exercise training over the course of the 12 weeks of study

participation. Minutes of moderate and vigorous intensity exercise training per week will be summed and used to assess moderate-intensity continuous exercise training and high-intensity interval training adherence.

2. Activity status: will be measured using the Duke Activity Status Index (DASI), a self-administered questionnaire comprising 12 questions that determines a persons' functional capacity. Higher scores represent greater functional capacity. The DASI is a validated measure that is highly correlated with objective measures (e.g. VO2peak).

3. Atrial fibrillation Specific Quality of life: will be measured using the University of Toronto Atrial Fibrillation Severity Scale (AFSS). The AFSS is a disease-specific quality of life measure used to capture subjective and objective ratings of disease burden in patients with atrial fibrillation. It consists of 19 items and assesses atrial fibrillation burden (4 items), health care utilization (4 items) and symptom severity (7 items). The AFSS has been tested according to standardized psychometric parameters of content validity, reliability and variability.

4. Symptom burden: will be measured using the Canadian Cardiovascular Society Severity of Atrial Fibrillation Scale (CCS-SAF). The CCS-SAF is a simple, concise, symptom-based severity scale to assess patient status. The CCS-SAF score is determined using 3 steps: 1) documentation of possible atrial fibrillation-related symptoms (palpitations, dyspnea, dizziness/syncope, chest pain, weakness/fatigue); 2) determination of symptom-rhythm correlation; and 3) assessment of the effect of these symptoms on patient daily function and quality of life. CCS-SAF scores range from 0 to 4, with highest values denoting severe impact of symptoms on quality of life and activities of daily living. The CCS-SAF has been validated in patients with atrial fibrillation.

5. Self-reported symptom frequency and severity: will be measured using the 7-day symptom diary. Symptoms attributed to atrial fibrillation are recorded on this diary as they occur. Date and time are noted along with the severity of each symptom; multiple pages will be available to accommodate patients with frequent symptoms. These symptoms will be recorded at baseline, and again at the end of the study.

6. Anxiety and depressive symptoms: will be measured using the Hospital Anxiety and Depression Scale (HADS). The HADS is a validated questionnaire, widely used in clinical settings and found to be a reliable instrument for detecting states of depression and anxiety, which is a common issue among patients with atrial fibrillation. It consists of two 7-point subscales of anxiety and depression.

7. Insomnia severity: will be measured using the Insomnia Severity Index. It is comprised of 7 questions used to assess the nature, severity and impact of insomnia. It has been demonstrated to be a reliable measurement tool and content validity was formally demonstrated via principal component analysis.

8. Sleep apnea risk: will be measured by the STOP-BANG Sleep Apnea Questionnaire. This is a 7-item validated questionnaire used to evaluate the risk of obstructive sleep apnea in patients. Sleep apnea is a common issue among patients with atrial fibrillation. Patients deemed at high risk for sleep apnea may be referred for a sleep assessment by [name] or [name].

9. Self reported sleep patterns: will be measured using a 7-day sleep diary. This will be used to capture any sleep problems and measure any progress in improving sleep. Details regarding sleep timing, quality, naps, alcohol consumption and sleep medication will be collected over a 7-day period.

10. Heart rate control: measured using 24-hour Holter ECG recordings and ECG recordings at each CPET.

11. Muscular fitness: measured using standard load tests. This test involves the completion of repetitions of leg press exercises, at a defined resistance of 40 kg at a cadence of 22 repetitions per minute (set by a metronome). The maximum number of repetitions done before falling behind the required cadence will be recorded.

12. Exercise capacity: measured using a gold standard symptom-limited, cardiopulmonary exercise test (CPET) on an electronically braked cycle ergometer using a ramp protocol. Gas exchange will be monitored continuously; the highest rate of oxygen uptake achieved (i.e. peak  $\text{VO}_2$  in mL/kg/min) during the last minute of the CPET will represent exercise capacity. All participants will be asked if they are willing to complete this measure at baseline and follow up and only those who are willing will complete it.

### **Additional Measures**

Cardio-respiratory fitness (measured at baseline only): will be evaluated during a symptom-limited, cardio-pulmonary exercise test on an electronically braked cycle ergometer using a ramp protocol. Peak power output will be evaluated during this exercise test and used for moderate-intensity continuous exercise training and high-intensity interval training exercise prescription. Whole-body  $\text{VO}_2$  will be measured using expired gas samples.

Body weight: will be measured using a digital scale to the nearest 0.1 kilogram during the baseline, intervention and follow up phases.

Waist circumference: will be measured using a tape measure during the baseline, intervention and follow up phases.

Fat mass: will be measured using bioelectrical impedance analysis during the baseline, intervention and follow up phases. Participants will be asked to follow the pretesting guidelines for bioelectrical analysis testing:

- No eating or drinking within 4 hours of the test
- No moderate or vigorous exercise within 12 hours of the test
- Void urine completely within 30 minutes of the test
- Abstain from alcohol consumption within 48 hours of the test
- Do not ingest diuretics, including caffeine before the assessment unless they are prescribed by a physician
- If you are in a stage of your menstrual cycle during which you perceive you are retaining water, postpone testing (female participants only)

Resting and exercise blood pressure: will be measured using a sphygmomanometer during the baseline and intervention as well as during the exercise training sessions.

Resting and exercise heart rate: will be measured manually or using polar heart rate monitors during the baseline and intervention phases as well as during the exercise training sessions.

Rating of perceived exertion: will be measure during the exercise tests and training sessions.

Gender-related data: will be measured using a set of questions related to gender identity, relations and roles. Participants will be given a paper copy which can be completed in person during their visit or alternatively it will be sent to their home address using a pre-paid envelope.

### **Analyses of Results**

Repeated measures mixed models analyses will be performed to examine changes in primary and secondary outcomes.

### **Risks, Benefits and Usual Standard of Care**

The usual standard of care for patients with persistent or permanent atrial fibrillation includes the following steps: 1) to make sure patient is well rate controlled, 2) to make sure patient is anti-coagulated if appropriate, and 3) if well rate controlled and anti-coagulated, then patient is discharged to family doctor. If patients choose to take part in this study, each participant will be asked to also complete the following: 1) screening, 2) baseline, and 3) 12-week exercise training program with repeated measures. These aspects of the study have been described in detail in the study protocol. No changes will occur to usual standard of care.

### **Risks of Participant**

Risks for usual standard of care:

Standard of care which consists of rate or rhythm control as well as anti-coagulation control significantly reduces the risk of stroke and decline in ventricular performance in patients with uncontrolled persistent or permanent atrial fibrillation. No changes will occur to usual standard of care.

Risks for research participants:

Participation in this study requires that participants perform exercise tests and training sessions. The risk of cardiovascular events during exercise testing varies directly with the incidence of cardiovascular disease. The risk of exercise testing is low, with approximately 6 cardiac events per 10,000 tests (0.06%). This is comparable to the usual care that patients in cardiovascular rehabilitation programs would receive. Recent studies have reported a rate of 1 cardiac arrest per 116,906 patient-hours, 1 myocardial infarction per 219,970 patient-hours, 1 fatality per 752,365 patient-hours, and 1 major complication per 81,670 patient-hours in a cardiovascular rehabilitation setting. It should be noted that these rates are low and likely due to the fact that patients in these studies were screened and exercised in a medically supervised setting equipped to handle emergencies. This is the case of the University of Ottawa Heart Institute, Division of Prevention and Rehabilitation.

The commonly reported side effects that may result from exercise testing and training sessions may include palpitation, chest pain, shortness of breath, headache, nausea and/or fatigue.

Participants may find the questionnaires regarding quality of life (Short Form 36, University of Toronto Atrial Fibrillation Severity Scale), symptom burden (Canadian Cardiovascular Society Severity of Atrial Fibrillation Scale), functional capacity (Duke Activity Status Index), anxiety and depression (Hospital Anxiety and Depression Scale, insomnia (Insomnia Severity Index) and sleep apnea (STOP-BANG Sleep Apnea Questionnaire) distressing.

### **Monitoring and Reporting of Adverse Events/Serious Adverse Events**

The following definitions have been approved as part of Good Clinical Practice in Research:

#### **Unanticipated Problem**

An unanticipated problem is defined as any incident, experience, or outcome that meets all of the following criteria:

Unexpected (in terms of nature, severity, or frequency) given (a) the research procedures that are described in the protocol-related documents, such as the REB-approved research protocol and informed consent document, or the Investigator Brochure (IB) or product monograph (PM); and (b) the characteristics of the research participant population being studied; and

Related or possibly related to participation in the research (possibly related means there is a reasonable possibility that the incident, experience, or outcome may have been caused by the [investigational product(s)] or procedures involved in the research); and

Suggests that the research places research participants or others at a greater risk of harm (including physical, psychological, economic, or social harm) than was previously known or recognized.

#### **Adverse event**

An adverse event is defined as any untoward medical occurrence in a research participant administered an investigational product and which does not necessarily have a causal relationship with this product. An AE can therefore be any unfavorable and unintended sign (including an abnormal laboratory finding, for example), symptom, or disease temporally associated with the use of an investigational product, whether or not related to the investigational product.

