#### **Serious Adverse Event**

To ensure no confusion or misunderstanding of the difference between the terms "serious" and "severe," which are not synonymous, the following note of clarification is provided:

The term "severe" is often used to describe the intensity (severity) of a specific event (as in mild, moderate, or severe myocardial infarction); the event itself, however, may be of relatively minor medical significance (such as severe headache).

This is not the same as "serious," which is based on patient/event outcome or action criteria usually associated with events that pose a threat to a patient's life or functioning.

Seriousness (not severity) serves as a guide for defining regulatory reporting obligations.

After reviewing the various regulatory and other definitions in use or under discussion elsewhere, the following definition is believed to encompass the spirit and meaning of them all:

*A serious adverse event (experience) or reaction is any untoward medical occurrence that at any dose:*

- results in death;
- is life-threatening;
- requires inpatient hospitalization or prolongation of existing hospitalization;
- results in persistent or significant disability/incapacity; or
- is a congenital anomaly/birth defect.

The term "life-threatening" in the definition of "serious" refers to an event in which the patient was at risk of death at the time of the event; it does not refer to an event which hypothetically might have caused death if it were more severe.

Medical and scientific judgment should be exercised in deciding whether expedited reporting is appropriate in other situations, such as important medical events that may not be immediately life-threatening or result in death or hospitalization but may jeopardize the patient or may require intervention to prevent one of the other outcomes listed in the definition above. These should also usually be considered serious.

Examples of such events are intensive treatment in an emergency room or at home for allergic bronchospasm; blood dyscrasias or convulsions that do not result in hospitalization; or development of drug dependency or drug abuse.

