All unanticipated problems/adverse events/serious adverse events will be recorded on the case report form (CRF) and in the source documents at the site of testing. A log for all unanticipated problems/adverse events/serious adverse events occurring in the study will be kept. The details of any unanticipated problems/adverse events/serious adverse events at each study visit, using the protocol-defined terminology, will be recorded.

The PI and or RC will educate the participants about unanticipated problems/adverse events/serious adverse events as well as the importance of reporting them to the study coordinator at study visits.

Anyone within the research team who becomes aware of unanticipated problems/adverse events/serious adverse events will report this to the PI. The PI will assess the unanticipated problems/adverse events/serious adverse event and provide the research participant with appropriate medical care as applicable. The PI will report to the REB within 7 days only the local adverse events/serious adverse events that are deemed to be unanticipated problems.

The monitoring of these unanticipated problems/adverse events/serious adverse will be made in accordance with the Ottawa Health Sciences Network Research Ethics Board's SOP 404.001 Ongoing REB Review Activities including the SOP 404 Adverse Event Reporting Requirements addendum.

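### The adverse event definition is tied to an investigational product that this exercise trial does not give, so expected non-serious harms of testing and training meet none of the protocol's event definitions

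*Protocol*

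**What the plan says.** The Protocol sets out three event terms under Monitoring and Reporting of Adverse Events/Serious Adverse Events.

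- **Adverse event.** The person covered is one given a product: "any untoward medical occurrence in a research participant administered an investigational product". The timing is also set by the product: "temporally associated with the use of an investigational product, whether or not related to the investigational product".
- **Serious adverse event.** The definition opens with "any untoward medical occurrence that at any dose" and then lists outcomes such as death, threat to life and hospitalization. Its examples of other important events include bronchospasm, blood dyscrasias and drug dependency.
- **Unanticipated problem.** The event must be unexpected, at least possibly related to the research, and suggestive of greater risk than was known. Related means that it "may have been caused by the [investigational product(s)] or procedures involved in the research". This is the only one of the three definitions that mentions procedures.

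The paragraphs after these definitions provide for a log of all such events in the study. They also say that event details at each visit, "using the protocol-defined terminology, will be recorded".

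The Intervention section describes two exercise programmes added to standard care. Risks of Participant says that the research risk comes from exercise tests and training sessions, and that their common side effects "may include palpitation, chest pain, shortness of breath, headache, nausea and/or fatigue".

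**The concern.** The wording belongs to a drug or device trial. Nothing in the Protocol says that exercise training or testing is to be read as the investigational product. The document therefore expects particular harms from its own tests and sessions, and then defines the term used to record harms in a way that does not reach them.

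What is at stake is the usefulness of the safety record. The trial compares intervals at 80-150% of peak power output with moderate continuous exercise in patients with atrial fibrillation. Staff who apply the definitions literally would have no category for an ordinary, anticipated, non-serious harm. Staff who ignore the literal wording must decide for themselves what counts. Some of the same symptoms are also collected as outcome data, through the symptom severity scale and the 7-day symptom diary, so a clear rule on when a symptom is also an adverse event has practical value.

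**Working it through.** No arithmetic applies: the point depends on no rate, effect size, significance level or sample size. The check is to take types of event and test each against the three definitions as written.

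**Case 1: palpitation or chest pain in a supervised session or exercise test, resolving without admission.**
- Adverse event: the participant must have been given an investigational product, and the event must be timed to its use. No product exists, so neither condition is met.
- Unanticipated problem: all three criteria are needed. Risks of Participant names this harm as a common effect of testing and training, so it is not unexpected in nature. Unless its severity or frequency goes beyond what was expected, it fails the first criterion.
- Serious adverse event: none of the listed outcomes occurs, and in the ordinary case it is not an important medical event of the kind described.
- Result: the event meets none of the three definitions.

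**Case 2: death, a life-threatening event or hospital admission after a session.**
- Serious adverse event: the definition starts from any untoward occurrence and turns on its outcome. The dose phrase has no referent here, but it does not say that a product must have been given.
- Result: the event is covered, although the wording fits badly.

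**Case 3: an unexpected, related, non-serious harm of a study procedure that points to greater risk than was known.**
- Unanticipated problem: met, through the reference to research procedures.
- Adverse event: not met, for the same reason as in Case 1.
- Result: covered by one definition only. The rule for reporting to the Research Ethics Board speaks of local adverse or serious adverse events that are judged to be unanticipated problems. On a literal reading this event is not in that starting set.

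The recording instruction refers staff back to the Protocol's own terms. That makes the adverse event wording operative. The gap in Case 1 falls on exactly the non-serious effects that the risk section lists.

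**The case against.** The best defence is that the section's purpose is plain. It calls for a log of everything that happens in the study, with recording at the site of testing, and the risk section names effects of exercise. The definitions are introduced as general Good Clinical Practice text, and the bracketed product reference under Unanticipated Problem looks like an unedited template slot. On this view the wording is a drafting residue that nobody would apply literally. An unanticipated problem is also a different concept from an adverse event, so a difference in scope between the two is not in itself a contradiction. Finally, the ethics board's procedure on adverse event reporting is cited and may cover trials without a product.

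Much of this stands. Practice may well be better than the text, and the difference between the two definitions shows poor fit rather than two rival rules. But the log is a log of adverse events, and that term is defined. An evident intention does not tell staff what counts. The content of the cited procedure cannot be checked from the Protocol.

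A reader might infer four stronger things that the document does not support.

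- **That serious harms of exercise are also excluded, so that the literal count of all events is zero.** The serious event definition contains no product condition.
- **That recording will differ between arms.** The same definitions, log and assessment by the investigator apply to both arms, and nothing in the text produces a difference by arm.
- **That the planned exposure measures the loss.** With 108 participants, two sessions a week and 12 weeks, there would be 108 × 2 × 12 = 2,592 supervised sessions at full attendance. That is exposure, and it says nothing about how many events would go unrecorded.
- **That the harm comparison is a stated aim.** Safety is not among the objectives, hypotheses or outcome measures. How events are tabulated by arm may properly be left to the statistical analysis plan.

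**Conclusion.** The point holds for the adverse event definition. As written it does not fit a trial without an investigational product, and the expected non-serious harms of testing and training satisfy none of the three definitions. This is a stated rule that fits badly, not a detail left for another document.

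The effect is limited to non-serious events. The serious event wording is ill-fitting but not exclusionary. The number of events affected, and any effect on a comparison of arms, cannot be derived from the Protocol.

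The conclusion assumes that the definitions are applied as worded and that no other study document treats exercise as the product. If staff already log every harm of training and testing, the amendment brings the text into line with practice.

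**What to change.** Amend the wording in two places.

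- **Adverse event.** Replace both product phrases (the one defining who is covered and the one setting the timing) with participation in the study procedures: study testing, supervised high-intensity interval or moderate-intensity continuous sessions, and encouraged home exercise. Keep the statement that an event counts whether or not it is related. This brings the definition into line with the procedures wording under Unanticipated Problem.
- **Serious adverse event.** Delete the reference to dose.

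State that the same definition applies in both arms, and that it runs from consent through the study's follow-up visits. It should not stop at week 12, because visits are planned at about week 26 and from year 1 to year 10, and a week-12 cut-off would narrow what the current plan for a study-wide log appears to intend.

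The cost is a short amendment and slightly more events to log. No clinical rule changes.
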